## Abstract

**Background:**

The psychosocial needs and risks of children with cancer and their families are well-documented including increased risk of parental distress, posttraumatic stress, and anxiety. There is a critical need to provide evidence-based psychosocial care to parents and caregivers of children with cancer. Digital health interventions are important to address many barriers to in-person intervention delivery but are not widely used in pediatric psychosocial cancer care. The COVID-19 pandemic has reinforced the need for flexible, acceptable, and accessible psychosocial digital health interventions. The Electronic Surviving Cancer Competently Intervention Program (eSCCIP) is an innovative digital health intervention for parents and caregivers of children with cancer, delivered through a combination of self-guided web-based content and supplemented by 3 telehealth follow-up sessions with a trained telehealth guide. A Spanish language adaptation of eSCCIP, El Programa Electronico de Intervencion para Superar Cancer Competentemente (eSCCIP-SP), has been developed. The self-guided web-based cores of eSCCIP/eSCCIP-SP are a mix of didactic video content, multifamily video discussion groups featuring parents of children with cancer, and hands-on web-based activities.

**Objective:**

The objective of this study is to test eSCCIP/eSCCIP-SP in a multisite randomized controlled trial, compared to an internet-based education control condition consisting of information specifically focused on concerns relevant to parents and caregivers of children with cancer.

**Methods:**

Using a randomized controlled clinical trial design, 350 eligible parents and caregivers of children with cancer will be randomly assigned to the intervention (eSCCIP/eSCCIP-SP) or an education control condition. Data will be collected at 3 time points: preintervention (prior to randomization), immediately post intervention (after 6 weeks), and at a 3-month follow-up (from baseline). Participants randomized to either condition will receive study material (eSCCIP/eSCCIP-SP intervention or education control website) in English or Spanish, based on the primary language spoken in the home and participant preference.

**Results:**

The primary study end point is a reduction in acute distress from baseline to postintervention, with secondary end points focused on reductions in symptoms of posttraumatic stress and anxiety, and improvements in coping self-efficacy and cognitive coping. An additional exploratory aim will be focused on implementation strategies and potential costs and cost-savings of eSCCIP/eSCCIP-SP, laying the groundwork for future trials focused on dissemination and implementation, stepped-care models, and intervention refinement.

**Conclusions:**

This trial will provide necessary data to evaluate the efficacy of eSCCIP/eSCCIP-SP. This intervention has the potential to be an easily scalable and highly impactful psychosocial treatment option for parents and caregivers of children with cancer.

**Trial Registration:**

ClinicalTrials.gov NCT05294302; https://clinicaltrials.gov/ct2/show/NCT05294302

**International Registered Report Identifier (IRRID):**

PRR1-10.2196/46339

## Introduction

### Background

Parents and caregivers of children with cancer are at risk for negative psychosocial sequelae following their child’s cancer diagnosis [1-3]; yet, few evidence-based options exist for improving psychosocial outcomes. This is particularly discouraging because the Standards for Psychosocial Care for Children with Cancer and Their Families specifically recommend that parents and caregivers of children with cancer have access to such interventions to decrease the risk of adverse psychosocial outcomes, including acute distress, posttraumatic stress symptoms (PTSSs), anxiety, depression, and decreased family functioning [1,4]. Parent, child, and family-level functioning are closely linked, and parent distress is linked to impaired family functioning and child maladjustment across the cancer trajectory [2,5-8]. Providing evidence-based psychosocial support to parents and caregivers of children with cancer is a clear, actionable strategy to prevent adverse outcomes and improve individual and family functioning following a pediatric cancer diagnosis [9,10].

Individuals identifying as Latinx represent the largest minority group in the United States and are also the fastest-growing segment of the population in the United States, representing 18% of the total population and contributing over half (52%) of the population’s growth between 2010 and 2019 [11]. Parents and caregivers of children with cancer, who are of Latinx descent, are at especially high risk for negative psychosocial sequelae because they are overrepresented in the United States in terms of being affected by multiple, negative, systemic, and sociodemographic factors, including low socioeconomic status and limited English proficiency [12]. Socioeconomic status has been found to mediate survival outcomes in pediatric cancer, with worse outcomes for Latinx and racially diverse children [13-15]. Moreover, parents and caregivers of children with cancer of Latinx descent often report high levels of distress following their child’s cancer diagnosis [12,13]. Although there is some evidence that culturally adapted interventions are effective in improving health and well-being outcomes for these populations [16-19], cultural and language adaptations of psychosocial evidence-based interventions for the Latinx population are scarce [1,12,20]. As the Latinx population in the United States continues to grow, there is an urgent need to provide evidence-based psychosocial care to this at-risk subset of parents and caregivers of children with cancer.

Access to technology and the internet is widespread in the United States and is often used to seek health care information and support [21,22]. Latinx and non-Latinx populations report internet use at comparably high levels, with recent data showing that 93% of White adults, 91% of Black adults, and 95% of Hispanic adults use the internet [23]. Trends in internet usage over time have demonstrated that the “digital divide” in the United States is shrinking across race and ethnicity, so the need for psychosocial interventions that adapt to this new reality is critical.

### Intervention Development and Adaptation

Several studies have laid the groundwork for the proposed randomized controlled trial (RCT). The Electronic Surviving Cancer Competently Intervention Program (eSCCIP) was developed as a brief, psychosocial digital health intervention for parents and caregivers of children with cancer to reduce negative psychosocial sequelae following pediatric cancer diagnosis and improve family functioning [24]. The theory and content of eSCCIP were adapted from 2 prior in-person interventions for parents and caregivers of children with cancer: the Surviving Cancer Competently Intervention Program [25] and the Surviving Cancer Competently Intervention Program—Newly Diagnosed [26]. To provide parents and caregivers of children with cancer with the accessibility and flexibility of a digital health intervention, eSCCIP was initially developed in 2015 using best practice methodology from the digital health literature. In addition to its foundation in both cognitive behavioral and family systems principles, eSCCIP is guided by the Ritterband Behavior Change model for internet interventions, which explains change as occurring through a pattern of unique, nonlinear interactions in 9 steps, including the users, the environment, and the web-based tool [27]. eSCCIP is further guided by the Pediatric Preventative Health Model [28,29], a social ecological model conceptualizing how families should receive psychosocial support based on individual needs, strengths, and risk factors. Following the conceptualization and initial development of eSCCIP, the intervention was refined using think aloud usability testing, collaboration with community stakeholders, and small-scale beta testing [24]. Recent preliminary studies evaluating the eSCCIP intervention have demonstrated high acceptability and feasibility, as well as preliminary evidence of efficacy [30]. Additional revisions and iterations have been made to eSCCIP to modernize and scale up for a larger RCT. To fill a critical need in the field, a Spanish-language adaptation of eSCCIP, El Programa Electronico de intervencion para Superar Cancer Competentemente (eSCCIP-SP) [31], was also developed using best practices for cultural and linguistic intervention development [32]. Refer to Figure 1 for a visual overview of the eSCCIP/eSCCIP-SP work to date.

**Figure 1 figure1:**
[figure not shown]
Overview of eSCCIP/eSCCIP-SP development. eSCCIP: Electronic Surviving Cancer Competently Intervention Program; eSCCIP-SP: El Programa Electronico de Intervencion para Superar Cancer Competentemente.

### Study Objectives

The purpose of this study is to test eSCCIP/eSCCIP-SP in a multisite RCT to build off existent pilot work and establish a strong base for the efficacy of the intervention. With the exception of the present intervention and a web-based adaptation of the Bright IDEAS Maternal Problem-Solving Skills Training Intervention [16,33,34], we are not aware of any additional psychosocial digital health interventions for parents and caregivers of children with cancer, so establishing a strong evidence base for this intervention is both timely and imperative in addressing the psychosocial needs in this population. The specific aims of this study are as follows:

Specific aim 1 evaluates the efficacy of eSCCIP/eSCCIP-SP in a multisite RCT comparing eSCCIP/eSCCIP-SP with an education control website in “real-world” clinical settings. The primary hypothesis is that eSCCIP/eSCCIP-SP will be more efficacious than an education control in decreasing acute distress post intervention. A secondary hypothesis is that eSCCIP/eSCCIP-SP will be more efficacious than an education control in decreasing PTSS and anxiety and improving coping self-efficacy and use of positive cognitive coping strategies post intervention.Specific aim 2 describes the patterns of user engagement and identifies clinical and psychosocial factors associated with eSCCIP/eSCCIP-SP treatment gains. A component of this aim is to identify clinical, demographic, and psychosocial protective factors and risks predictive of maximum eSCCIP/eSCCIP-SP participation benefit. Potential differences in outcomes for English-speaking and Spanish-speaking parents and caregivers of children with cancer will also be explored.Specific aim 3 explores preliminary eSCCIP/eSCCIP-SP implementation strategies and costs and cost savings. We will conduct qualitative interviews with oncology health care providers (psychosocial and medical/nursing staff) and intervention participants using the Consolidated Framework for Implementation Research (CFIR) paradigm to identify barriers and facilitators of eSCCIP/eSCCIP-SP uptake and completion. We will also estimate the costs and potential cost savings of delivering eSCCIP/eSCCIP-SP.

## Methods

### Ethics Approval

The MD Anderson Cancer Center Office of Human Subjects Protection serves as the central institutional review board for this study. Study procedures have been approved (protocol # 2021-0988).

### Study Design

This study is a multisite RCT that will enroll participants at 3 geographically diverse pediatric hospitals, which are subsequently anonymized as sites A, B, and C. Participants will be randomized to one of two treatment conditions: (1) eSCCIP/eSCCIP-SP (depending on primary language or preference) or (2) education control.

### Randomization

Randomization will be conducted at the family level according to a 1:1 ratio between groups, in permuted blocks of 6, stratified by site and language preference. The study data analyst at site A will use an Excel (Microsoft Corp) spreadsheet with a randomization scheme created by the study biostatistician to randomize families. This spreadsheet will be inaccessible to any members of the study team aside from the data analyst. It is not possible for study telehealth guides to be blinded to the intervention condition because of the in-person contact required for eSCCIP/eSCCIP-SP; however, study investigators and research coordinators (RCs) not involved in intervention delivery will not have access to random assignment information. After randomization, participants will be instructed on the procedures within their assigned group. All outcome measures will be completed directly on the web by study participants, further reducing the risk of bias.

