### Sample Size

Based on the power analyses discussed below, 350 parents and caregivers of children with cancer will be recruited to account for a conservative 25% attrition rate. Of note, although multiple caregivers from each family are eligible to participate, the target sample size of 350 parents and caregivers of children with cancer refers specifically to 350 primary participating caregivers from unique families. Data from nonprimary participating parents will be used only for exploratory analyses. Based on the results from pilot studies, we expect approximately 20% of the 350 families recruited to include a second participating parents and caregivers of children with cancer. Recruitment, retention, and engagement strategies have been an explicit focus of previous eSCCIP research, and strategies generated from this research and the literature inform the recruitment plan [35,36]. Recruitment targets are feasible based on the number of children with cancer treated annually at sites A, B, and C (1000 per year across sites), as well as the number of English-speaking and Spanish-speaking parents and caregivers of children with cancer at each site. We expect 40%-50% of the sample to be Spanish-speaking parents and caregivers of children with cancer. Previous eSCCIP studies have had high recruitment rates (64%-70%) [24,36] as well as retention rates of over 70% in eSCCIP pilot work. Estimating 25% study attrition is an appropriately conservative approach; however, recruitment targets will be evaluated frequently and adjusted accordingly if attrition is higher than expected, given previous work.

To specifically address aim 3, parents and caregivers of children with cancer will be identified from each study site using purposive sampling across demographic groups. We will initially target 10 participants from each site (n=30), comprising 6 parents and caregivers of children with cancer (3 English-speaking and 3 Spanish-speaking), 2 psychosocial providers, and 2 oncology providers, but final recruitment will be dependent upon data saturation. We will complete interviews until no new ideas are shared, consistent with best practices for reaching saturation in qualitative research [37].

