### Study Procedure

Potential participants will be screened for eligibility using a brief, web-based screening questionnaire that is accessible by direct contact with a member of the study team or through the study interest website. Once screened, an RC will confirm eligibility and instruct participants about the consent process. Web-based consent procedures will be conducted via DocuSign or a similar secure software. Once web-based consent is complete, participants will receive a unique username and password to log onto their randomized condition (eSCCIP/eSCCIP-SP or education control). Study questionnaires will be completed through this web platform. As there are no required components of the education control, automated or RC-directed text and email reminders to use the program will not be required for individuals randomized to the education control.

After completion of the initial web-based assessment battery, participants in the intervention condition will schedule their initial telehealth session using an automated scheduling tool available through the platform hosting eSCCIP/eSCCIP-SP. Participants will be notified that the overview core and core 1 need to be completed prior to the telehealth session. Automated reminders will be sent at regular intervals to encourage participation in study cores. Manual follow-up by RCs will also be initiated in cores that are not completed. Cores will automatically unlock at 1-week intervals, and telehealth sessions will be scheduled directly with the participant. A total intervention completion window of 4-6 weeks will be anticipated by the study team for each participant, building in some additional time for start-up and potential scheduling delays. A similar process has been successfully implemented in eSCCIP pilot studies [24,30]. Because eSCCIP/eSCCIP-SP cores and the education control website are delivered digitally, all parents and caregivers of children with cancer will have convenient access to their respective condition’s content anywhere the internet is available.

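### A single published block size of 6, with coordinators given both enrolment and eSCCIP-only core follow-up and no stated separation, leaves allocation concealment unsecured

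*Protocol article*

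**What the plan says.** - **Unit and ratio** (Protocol article, Randomization): "Randomization will be conducted at the family level according to a 1:1 ratio between groups".
- **Blocks and strata** (same section): "in permuted blocks of 6, stratified by site and language preference". Under Study Design the trial "will enroll participants at 3 geographically diverse pediatric hospitals", so three sites and two languages make six strata.
- **Who holds the list** (Randomization): a data analyst at site A. "This spreadsheet will be inaccessible to any members of the study team aside from the data analyst".
- **Masking of staff** (Randomization, repeated in substance under Limitations): guides cannot be blinded, but "study investigators and research coordinators (RCs) not involved in intervention delivery will not have access to random assignment information".
- **RC duties before randomisation** (Study Procedure): "an RC will confirm eligibility and instruct participants about the consent process".
- **RC duties after randomisation** (same section): "Manual follow-up by RCs will also be initiated in cores that are not completed". Cores belong to eSCCIP/eSCCIP-SP alone, and the section says that prompts to use the programme are not needed in the education control arm.

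The article does not say whether the RCs who enrol and the RCs who chase cores are the same people or different people.

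**The concern.** Giving the list to one analyst hides the list but not its pattern. With one known block size, a person who sees earlier assignments in a stratum can work out some of the later ones. An RC who chases an unfinished core knows that this family is in the intervention arm. If the same RC confirms eligibility and guides consent for the next family in that site and language, the enrolment decision is no longer made blind to the likely assignment.

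The masking statement does not close this gap. It protects only RCs outside intervention delivery, and the article does not place the enrolling RCs inside or outside that group.

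The stake is selection bias through the timing or steering of enrolment. It matters here because participants report the primary outcome (K-6 distress) themselves and know which programme they are using. Concealed allocation is therefore one of the main protections left.

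**Working it through.** **The plan's own figures.** The article gives no predictability figure. Its sample size reproduces and is not in dispute. With a standardised difference of 0.3, pre-post correlation 0.5, two-sided 5% and 80% power, n = 2 × (1.960 + 0.842)² × (1 − 0.5²) / 0.3² ≈ 131 per arm. Dividing by 0.75 for attrition gives 175 per arm, 350 in total.

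**Predictability within one block of 6 (three per arm, 20 equally likely orders).** The guesser knows the block size and the first k allocations, and names the arm with more places left.

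| k known | P(next is certain) | P(best guess is right) |
|---|---|---|
| 0 | 0 | 0.5 |
| 1 | 0 | 3/5 = 0.6 |
| 2 | 0 | 0.4 × 3/4 + 0.6 × 1/2 = 0.6 |
| 3 | 2/20 = 0.1 | 0.1 × 1 + 0.9 × 2/3 = 0.7 |
| 4 | 8/20 = 0.4 | 0.4 × 1 + 0.6 × 1/2 = 0.7 |
| 5 | 1 | 1 |

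**All earlier assignments known.** Certain: 0.1 + 0.4 + 1 = 1.5 of 6 = 25%, or about 87 of 350 families. Guessed: 0.5 + 0.6 + 0.6 + 0.7 + 0.7 + 1 = 4.1 of 6 = 68.3%. The closed forms agree: 2b/(b + 1) = 1.5 and b + 2^(2b−1)/C(2b, b) − 0.5 = 3 + 32/20 − 0.5 = 4.1, with b = 3.

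**Latest assignments unknown.** Each position then uses an earlier row of the table.

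| Latest unknown | Certain | Best guess right |
|---|---|---|
| 0 | 1.5/6 = 25% | 4.1/6 = 68.3% |
| 1 | 0.5/6 = 8.3% | 3.6/6 = 60.0% |
| 2 | 0.1/6 = 1.7% | 3.4/6 = 56.7% |
| 3 | 0% | 3.2/6 = 53.3% |

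**Which row is plausible.** The Sample Size section states "We expect 40%-50% of the sample to be Spanish-speaking", and recruitment runs for 3 years. Assuming equal sites, a Spanish-language stratum takes 350 × 0.40/3 ≈ 47 to 350 × 0.50/3 ≈ 58 families, which is one every 2.7 to 3.4 weeks. Cores unlock weekly and the expected completion window is 4 to 6 weeks. An RC who learns an assignment within a few weeks lags by about 0 to 1 allocation. One who learns it only at the end of the window lags by about 4/3.4 ≈ 1.2 to 6/2.7 ≈ 2.2.

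**Effect of varying the block size.** A simulation used 58 families per stratum, 3,000 runs, and an optimal guesser who knows the set of sizes, the starting point and all past assignments, but not the size of each block. Fixed blocks of 6 gave 23.5% certain and 67.7% guessed, slightly below the figures above because the last block is unfinished. Sizes drawn at random from 4, 6 and 8 gave 2.2% certain and 67.7% guessed.

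**The case against.** A reader might infer that the coordinators who enrol families do learn assignments by chasing cores. The article does not support that. It speaks of one RC for eligibility and of RCs in general for core follow-up, and its masking sentence implies that some RCs stand outside delivery. If those are the enrolling RCs, concealment holds. Who does which task is also the kind of detail that a full protocol may settle. This stands: the defect is an unstated separation, not a demonstrated breach.

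A reader might also infer that a quarter of allocations will in practice be known in advance. That is not supported either. The 25% and 68% need every earlier assignment in the block, and core chasing does not supply that. It directly reveals only intervention families with unfinished cores. A prompt intervention family and a control family look alike, because neither is chased. Guides and participants know assignments, but nothing says that guides enrol families or pass assignments to those who do. This also stands, so each figure above is an upper bound for its lag.

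The scope for steering is limited too. Screening is a web questionnaire that families can reach through the study interest website, and eligibility is broad. The ANCOVA adjusts for baseline K-6, which would reduce bias from selecting on distress. It would not remove bias from traits that are not in the model, such as motivation.

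None of this removes the remaining point. The single block size is a stated choice, it is public, and the RC duties are not reconciled with the masking sentence.

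**Conclusion.** The point holds in a conditional form. The article fixes and publishes one block size of 6 within six strata, and it gives the RC role both enrolment and follow-up of intervention-only cores with no stated separation. Allocation concealment is therefore not secured, though nothing shows that it has failed.

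The size depends on what an enrolling RC knows. It is at most 25% certain and 68% guessable with full knowledge, 8% and 60% with the latest assignment unknown, and 2% and 57% with the latest two unknown. The accrual estimate that makes a short lag plausible assumes equal recruitment across sites. The block size alone predicts nothing without knowledge of past assignments, so separating the roles matters more than changing the blocks. The planned 350 families are unaffected.

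**What to change.** 1. **Separate the roles (the more important step).** State under Randomization and Study Procedure that RCs who screen and consent do no core follow-up and see no assignments. Leave manual follow-up to other RCs who are already unmasked, alongside the automated reminders. This keeps the close tracking that the Limitations section credits for retention.
2. **Change the list for the remaining allocations.** Have the biostatistician draw block sizes at random, for example from 4, 6 and 8, within site and language. Keep the sizes from site staff and out of public documents. This cuts certain allocations to about 2%. It leaves the best-guess rate near 68% for anyone who knows all past assignments, so it cannot replace the first step.

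**Cost:** a new list, a division of RC duties at each site, and a possible within-stratum imbalance of 4 rather than 3 in an unfinished block.
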